## Abstract

**Background:**

Patients in acute care wards who deteriorate and are emergently transferred to intensive care units (ICUs) have poor outcomes. Early identification of patients who are decompensating might allow for earlier clinical intervention and reduced morbidity and mortality. Advances in bedside continuous predictive analytics monitoring (ie, artificial intelligence [AI]–based risk prediction) have made complex data easily available to health care providers and have provided early warning of potentially catastrophic clinical events. We present a dynamic, visual, predictive analytics monitoring tool that integrates real-time bedside telemetric physiologic data into robust clinical models to estimate and communicate risk of imminent events. This tool, Continuous Monitoring of Event Trajectories (CoMET), has been shown in retrospective observational studies to predict clinical decompensation on the acute care ward. There is a need to more definitively study this advanced predictive analytics or AI monitoring system in a prospective, randomized controlled, clinical trial.

**Objective:**

The goal of this trial is to determine the impact of an AI-based visual risk analytic, CoMET, on improving patient outcomes related to clinical deterioration, response time to proactive clinical action, and costs to the health care system.

**Methods:**

We propose a cluster randomized controlled trial to test the impact of using the CoMET display in an acute care cardiology and cardiothoracic surgery hospital floor. The number of admissions to a room undergoing cluster randomization was estimated to be 10,424 over the 20-month study period. Cluster randomization based on bed number will occur every 2 months. The intervention cluster will have the CoMET score displayed (along with standard of care), while the usual care group will receive standard of care only.

**Results:**

The primary outcome will be hours free from events of clinical deterioration. Hours of acute clinical events are defined as time when one or more of the following occur: emergent ICU transfer, emergent surgery prior to ICU transfer, cardiac arrest prior to ICU transfer, emergent intubation, or death. The clinical trial began randomization in January 2021.

**Conclusions:**

Very few AI-based health analytics have been translated from algorithm to real-world use. This study will use robust, prospective, randomized controlled, clinical trial methodology to assess the effectiveness of an advanced AI predictive analytics monitoring system in incorporating real-time telemetric data for identifying clinical deterioration on acute care wards. This analysis will strengthen the ability of health care organizations to evolve as learning health systems, in which bioinformatics data are applied to improve patient outcomes by incorporating AI into knowledge tools that are successfully integrated into clinical practice by health care providers.

**Trial Registration:**

ClinicalTrials.gov NCT04359641; https://clinicaltrials.gov/ct2/show/NCT04359641

**International Registered Report Identifier (IRRID):**

DERR1-10.2196/29631

## Introduction

Patients in acute care wards who deteriorate and are emergently transferred to the intensive care unit (ICU) have poor outcomes [1-6]. Subacute illnesses, such as sepsis, hemorrhage, and respiratory decompensation, occur in 5% or more patients and result in significant increases in length of stay and mortality [7]. Although potentially catastrophic, these subacute illnesses can be mitigated or indeed avoided depending on timely decisions made by the care team. Simply paying greater attention to patients who may be deteriorating from imminent changes in physiological status can allow for earlier clinical action and care to be appropriately escalated [8,9]. Informing clinicians of those patients at greater risk for otherwise unexpected clinical deterioration rather than waiting until after the common vital signs become noticeably abnormal and usual care alarms are triggered may provide a window for treatment that is more effective. Nurses’ worry or concern often precedes obvious deterioration in vital signs, suggesting that quantification of “concern” might lead to detection at an early stage when intervention may be more effective [10].

Advances in continuous bedside monitoring technology make a wealth of data available to assist evaluation by health care providers [11]. These data form the foundation for computational algorithms (artificial intelligence [AI]) that integrate real-time telemetric physiologic data to provide early warning of potentially catastrophic clinical events, including sepsis, emergent intubation, hemorrhage, and other events of clinical deterioration [12,13]. We have found subtle physiologic signatures of illness that are detectable through advanced mathematical analysis of cardiorespiratory dynamics trends up to 24 hours in advance of overt clinical deterioration [12,14-17]. Continuous predictive analytics monitoring involves advanced mathematical analysis of data from a variety of inputs (including parameters derived from telemetric monitoring) into an estimate of fold increase of risk that clinicians can observe in real time in a streaming environment [18,19].

In the neonatal setting, Griffin and Moorman [20] detected abnormal heart rate characteristics in the hours preceding a clinical diagnosis of sepsis and developed methods to process, characterize, and synthesize unprocessed cardiorespiratory monitoring data into a computational model that produced an estimation of risk. When these risk scores were visually displayed in the intervention arm of a multicenter randomized clinical trial of over 3000 very low birth weight neonates, there was a 20% decrease in mortality [21,22]. Thus, we know that early detection of deterioration improves outcomes, cardiorespiratory monitoring data are readily available, and trend-based models adding continuous monitoring outperform static vital sign models. We do not know, however, if displaying these visual AI risk scores can impact outcomes in adult patients of a variety of ages and historical comorbidities, who are susceptible to an array of adverse outcomes, as it does the outcomes in premature infants susceptible to sepsis.

Here, a cluster randomized controlled trial (NCT04359641) will test the use of Continuous Monitoring of Event Trajectories (CoMET; Figure 1), an AI-based visual analytic that dynamically displays risk estimates every 15 minutes for multiple adverse outcomes. CoMET uses continuous cardiorespiratory monitoring data and waveforms sampled every 2 seconds to perform mathematical measurements, such as measures of entropy and heart rate variability. R-R intervals and electrocardiogram-derived breathing rate were obtained from 200-Hz electrocardiogram waveforms; laboratory data and nurse-entered vital signs were obtained from the electronic medical records. These are used to derive an estimate of the fold increase in the risk of clinical deterioration. The models that have informed CoMET development have been described previously [7,12,18,23]. We expect that having access to a visual risk analytic for impending catastrophic outcomes will draw the clinicians’ attention to those patients who warrant early or extra consideration. For example, those patients with a higher risk score for short-term crises may be prioritized for assessment during daily rounds. This study will test the use of the CoMET display on patient outcomes, the time to proactive clinical action, and the associated costs to the health care system.

**Figure 1 figure1:**
[figure not shown]
CoMET artificial intelligence–based visual risk analytic. CoMET: Continuous Monitoring of Event Trajectories.

## Methods

### Overall Design

We will be conducting a parallel, cluster randomized controlled trial (RCT). All patients who are admitted to an 85-bed acute care cardiology medical-surgical floor will be enrolled in the study. In June 2020, institutional review board approval was granted for the Predictive Monitoring-Impact in Acute Care Cardiology Trial (PM-IMPACCT) along with waiver of informed consent, given the minimal risk nature of the study protocol. Clusters will be defined by room number, and upon enrollment, patients will be assigned to either intervention (CoMET display) or usual care (standard of care). The intervention will consist of CoMET display and charting in electronic medical records, mention of CoMET score on rounds, and standard of care cardiorespiratory monitoring when ordered. Meanwhile, usual care will consist of standard of care cardiorespiratory monitoring when ordered and no CoMET score displayed, charted, or mentioned on rounds. The study period will be 20 months. This report follows the SPIRIT (Standard Protocol Items: Recommendations for Interventional Trials) reporting guideline [24].

### Intervention Details

Data will be automatically collected electronically in real time for all patients (intervention and usual care) admitted to the randomized beds on the cardiology floor. The CoMET server is hosted within the hospital information technology environment and interfaces with the hospital interface engine to automatically gather clinical information, including numerical values in flow sheets, laboratory results, and continuous cardiorespiratory monitoring data [25]. For the intervention group only, the scores will then be displayed on monitors in real time and will be updated every 15 minutes.

Clinical research coordinators will routinely be present on inpatient rounding to bring up the web-based version of the CoMET display for the intervention arm and discuss relevant trends and answer questions about CoMET interpretation. Nurses will be asked to assess CoMET scores as part of routine vital sign collection. Every hour, the CoMET scores flow through directly to the electronic medical record vital sign flowsheet. Assessment protocol guidelines in response to CoMET scores on the intervention arm will suggest that if the CoMET score rises by 2 or more within a period of 3 hours, a nurse should assess the patient and consider alerting the nurse practitioner or resident physician caring for that patient. There is no direct clinical action or response mandated as a part of this RCT*.*

### Inclusion and Exclusion Criteria

All patients admitted to one of the 85 beds in 56 rooms on the acute care cardiology medical-surgical and cardiothoracic surgery floor (which encompasses a floor of the University of Virginia Medical Center and is further divided into 3 wards) will be enrolled in this study.

### Randomization Process

The room and bed in which a patient is placed is based on standard of care. The rooms are being cluster randomized to either intervention or usual care. The assignment of patients to rooms will not be influenced by the randomization status of the room.

There will be 14 clusters containing an average of 4 rooms (6 beds) each, with the aim of maintaining balance across wards and units (intermediate care unit, transplant, or neither). Clusters will be rerandomized every 2 months following a replicated Latin square design within each stratum to ensure balanced treatment assignment within each time period and over the length of the study. Randomization will be performed using the randomization inference package in R (The R Foundation for Statistical Computing). The randomization will be masked until it is implemented every 2 months. Postimplementation, the randomization will not masked or blinded because it will be clear to anyone in the hall or central station which beds have a CoMET score displayed and which do not. Future randomization assignments will only be known by the study statistician (SR) and those technical personnel implementing CoMET at the time that randomization changes (MC).

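### Choosing a bed is what allocates a patient, each room's arm is openly visible for 2 months, and no step described secures placement that is independent of arm

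*Protocol article*

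**What the plan says.** All references are to the Methods of the protocol article.

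- **Entry.** Inclusion and Exclusion Criteria enrols "All patients admitted to one of the 85 beds in 56 rooms" on the floor. There is no further eligibility step.
- **Allocation.** Overall Design states: "Clusters will be defined by room number, and upon enrollment, patients will be assigned to either intervention (CoMET display) or usual care". The room has its arm before the patient arrives.
- **Placement.** Randomization Process states: "The room and bed in which a patient is placed is based on standard of care". It adds: "The assignment of patients to rooms will not be influenced by the randomization status of the room".
- **Masking.** The same section states: "The randomization will be masked until it is implemented every 2 months". After that, "it will be clear to anyone in the hall or central station which beds have a CoMET score displayed and which do not". Only upcoming assignments are held back, by the study statistician and the technical staff who implement them.
- **Structure.** "There will be 14 clusters containing an average of 4 rooms (6 beds) each", balanced over wards and unit types and rerandomized every 2 months.
- **Data.** Intervention Details states: "Data will be automatically collected electronically in real time for all patients (intervention and usual care) admitted to the randomized beds".
- **Moves.** The Primary Hypothesis section censors a patient, with no event observed, at a change of bed. It also allows that a patient who has an event and returns to the ward may do so in a different arm.

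**The concern.** Randomizing rooms balances rooms. It balances patients only if they reach rooms independently of arm. Here allocation happens when a bed is chosen, after the arm has been fixed and made visible, so concealment of allocation is absent at the moment it matters. The independence that the comparison needs is stated as an outcome, and no described procedure produces it.

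There is a plausible motive. Clinicians are taught throughout the study that the display draws attention to patients with early signs of deterioration, so someone with a say in placement might prefer a displayed room for a worrying patient. There are three possible routes:

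1. First placement on arrival.
2. Placement again when a patient returns to the ward after an event.
3. A move within the floor. Because a bed change censors, a worrying usual-care patient who is moved leaves usual care before any event counts there.

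If higher-risk patients drift toward displayed rooms, the display looks less beneficial than it is, or harmful. Drift the other way flatters it. The Poisson generalized estimating equation (GEE) described for the primary outcome handles correlation and differing time at risk. It does not correct a difference in patient risk between arms.

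**Working it through.** **1. The plan's own figures.** 56 / 14 = 4.0 rooms and 85 / 14 = 6.07 beds per cluster, as stated. 20 / 2 = 10 periods, so 14 × 10 = 140 cluster-periods and 10,424 / 140 = about 74 admissions in each. The 10,424 is given as an estimate of admissions. It cannot be rebuilt as a sample size, because the article gives no effect size, event rate or intracluster correlation for the primary outcome. This point disputes no stated figure.

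**2. Inputs for an illustration.**

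- From the article: 10,424 admissions, 11% attrition, final nominal alpha .047.
- Assumed: 5% event rate. The Introduction gives 5% or more for subacute illnesses, which is not this trial's composite.
- Assumed: 10% of admissions are high risk with a 20% event rate. The rest then have (0.05 − 0.10 × 0.20) / 0.90 = 3.33%.
- Assumed: the display has no effect, and a share p of high-risk patients goes to displayed rooms.
- Assumed: a two-sided test of proportions (the primary outcome is event-free hours, so this shows scale only).
- Assumed: design effect 1 to 1.75. The upper value corresponds to an intracluster correlation near 0.01 at 74 per cluster-period.

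**3. Spurious contrast.** Display rate = (0.10 × p × 0.20 + 0.45 × 0.0333) / (0.10 × p + 0.45). Usual care uses 1 − p.

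| p | Display | Usual care | Risk ratio |
|---|---|---|---|
| 0.525 | 0.0255 / 0.5025 = 5.07% | 0.0245 / 0.4975 = 4.92% | 1.03 |
| 0.55 | 0.0260 / 0.505 = 5.15% | 0.0240 / 0.495 = 4.85% | 1.06 |
| 0.60 | 0.0270 / 0.510 = 5.29% | 0.0230 / 0.490 = 4.69% | 1.13 |

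**4. Effect on the test.** Analysed patients: 10,424 × 0.89 = 9,277, about 4,639 per arm.

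- At p = 0.55 the arms hold 4,685 and 4,592. The standard error is √[0.05 × 0.95 × (1/4,685 + 1/4,592)] = 0.00453, and the shift is 0.0030 / 0.00453 = 0.66. Against the critical value 1.986, a display with no effect is declared different with probability about 0.10, or 0.075 at design effect 1.75. Nominal is .047.
- At p = 0.60 the same steps give about 0.26 and 0.16.
- Power also falls. At design effect 1, a true risk ratio of 0.76 (0.759 unrounded) has 80% power without selection. At p = 0.55 the display rate becomes 0.759 × 5.15% = 3.91%. The standard error is √[0.0391 × 0.9609/4,685 + 0.0485 × 0.9515/4,592] = 0.00425. Then (0.0485 − 0.0391) / 0.00425 − 1.986 = about 0.23, which is about 59% power.

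**5. Sensitivity to the mix.** Suppose instead that 20% of admissions are high risk with a 15% event rate and the rest have 2.5% (again 5% overall). Swap patients so that the arms stay equal in size.

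| High-risk split | Patients swapped | Risk ratio | Rejection rate, no true effect |
|---|---|---|---|
| 51/49 | 19 | 1.02 | 0.050–0.052 |
| 52.5/47.5 | 46 | 1.05 | 0.066–0.081 |
| 55/45 | 93 | 1.11 | 0.13–0.19 |

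A small departure does little. A sustained one of 5 to 10 points in p begins to matter.

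**The case against.** **The article condenses a fuller protocol.** Bed-assignment procedures, balance reports and sensitivity analyses may sit in documents not shown, and their absence here is not in itself a fault. That stands. What remains is what the article does state: the arm is fixed first, patients are then placed, the arm is open to view, and masking covers future assignments only. Those features create the exposure whatever is written elsewhere.

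**The stated protections are real.** Enrolling every admission under a consent waiver removes selection by consent. Balance over wards and unit types, with rerandomization every 2 months, limits confounding by room type. Neither prevents a choice between open rooms of opposite arms in the same ward.

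**Three stronger readings are tempting and are not supported.**

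- A reader might infer that floor staff choose beds and will favour displayed rooms. The article does not say who assigns beds or whether they see the arm, and it shows no selection.
- A reader might infer that such bias would go undetected, or that a null result could never be told apart from it. Data are collected electronically in both arms, and Outcome Ascertainment and Event Adjudication describes bulk extraction of laboratory values, timestamps and room transfers. A comparison of entry risk and moves is therefore feasible, even afterwards.
- A reader might infer that every patient has a CoMET score on arrival in both arms. The article says that data are collected for all, but cardiorespiratory monitoring is used only when ordered, so some scores may be missing.

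**The magnitude is not evidence about this trial.** That also stands. The risk mix and the splits are assumptions.

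**Conclusion.** The point holds as a design weakness, not as a demonstrated bias. The validity of the primary comparison depends on placement being independent of arm. The article asserts that independence while describing a visible arm and no step that secures it.

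The size is unknown. Under the main assumed mix, a 55/45 to 60/40 split of high-risk patients yields a spurious risk ratio of about 1.06 to 1.13. Under the alternative mix, 55/45 yields about 1.11. In both, a split near 51/49 is of little consequence. For scale, the risk ratio detectable with 80% power at a 5% event rate is about 0.76 to 0.69 for design effects 1 to 1.75, so the larger splits are not negligible beside the effect sought. The direction depends on which arm receives the higher-risk patients.

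The change is worth making because it is cheap and protects the primary comparison.

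**What to change.** 1. **Placement.** State who assigns beds and whether they can see the arm. Keep the arm out of the information used to assign beds. Placement continues by standard of care, without reference to arm.
2. **Monitoring.** For each 2-month period, the study statistician compares arms within ward and unit strata on number of arrivals, source of arrival and entry risk (first available CoMET score, or its inputs). The report also tabulates moves within the floor by direction, usual care to display and the reverse. It goes to the DSMB as a description. A significance trigger is best avoided: several variables over 10 periods and several strata would set it off by chance.
3. **Analysis.** Prespecify a primary-outcome analysis adjusted for entry risk and report it beside the main result whatever the balance looks like. Making the adjustment conditional on an observed imbalance would make the analysis depend on the data.

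The cost is some protocol wording, one report per period from data already collected, and one further model. Entry scores will be missing for some patients whose monitoring was not ordered, so the inputs that are available must be named in advance. People on the floor will still see the arm, so these steps reduce and measure the bias without eliminating it.

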### Implementation and Education Considerations for Clinicians

All clinicians will be educated about CoMET to follow assessment guidelines in response to CoMET score. With consideration to alert fatigue, an increase of 2 or more within a period of 3 hours was selected as a guideline for assessment. In our retrospective cohort, a rise >2 units occurs 2 to 3 times per ward per day. On average then, a single nurse may experience 1 CoMET rise alert every 3 shifts. The clinicians will be provided education about what a score rising on either (or both) axes represents and the differential diagnoses to consider. This approach leaves the clinical context to that of the clinician and does not specify the specific diagnostics to order. The purpose of CoMET is to alert clinicians to prodromes or subtle physiological changes that precede overt clinical signs and draw attention to patients who may be in need of further attention, further clinical diagnostics, or escalation in care delivery. Clinicians may choose to draw a blood culture, initiate a rapid response team call, initiate oxygen therapy, or to do nothing but closely monitor or reassess the patient in an hour. Because CoMET models are trained on multiple events of clinical deterioration, clinicians understand the context of the CoMET score within the larger patient trajectory. There will be continual engagement and re-education throughout the entire study period across all clinician groups.

### Study Outcomes and Statistical Analysis

#### Primary Hypothesis

The primary hypothesis is that display of predictive analytics monitoring on acute care cardiology wards increases the number of hours free from clinical deterioration.

The primary outcome is the number of hours free from clinical deterioration (acute clinical events) within 21 days of admission. Hours of acute clinical events are defined as the time when one or more of the variables found in Textbox 1 occur. A maximum score will be 21 event-free days (504 hours). Patients who are discharged from the hospital prior to 21 days without an event will be counted as having 21 event-free days (504 hours). Patients who die during the admission will be counted as having 0 event-free days (0 hours). As an example, a patient who has an emergent ICU transfer on hour 26 of their admission will have 25 event-free hours. Patients will be censored (with no event observed) at the time of nonemergent ICU transfer (ie, for planned bronchoscopy), nonemergent surgery transfer, or other transfer (change in bed assignment) because a change in bed assignment can result in a change in randomization allocation (as carry over could occur in patients who have a display and then become “undisplayed”). We will conduct a randomized (formerly called “intent-to-treat”) analysis, in which all available data on all randomized participants are included for the primary end point comparison between intervention and usual care.

For the primary outcome (hours free of an acute clinical event), the primary analysis will employ a generalized estimating equation (GEE) with Poisson link. This model will be able to handle the multiple levels of correlation in the study design—patients within a cluster and potentially different intervention arms within a patient who has an event and then returns to the ward—as well as differences in the amount of time at risk for each patient that is censored.

Study outcomes by hypotheses.

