**Hypotheses 2 and 4**
1. Proportions of the following individual events at any point in the hospital stay after admission to the fourth floor:Emergent ICU transfer (emergent defined as urgent, unplanned)Emergent intubation (emergent is defined by clinician’s notes as a nonplanned procedure)3 units or more of blood ordered in 24 hoursinotropes or vasopressor useShock requiring inotropes or vasopressorsSepsis (sepsis-2 definition)Septic shock requiring inotropes or pressors (defined by a combination of the 2 above criteria)Cardiac arrestDeathDiuretic drip indicating congestive heart failure escalationInotropes or pressors for heart failureEmergent surgery prior to ICU transfer (emergent is defined by clinician’s notes as a nonplanned procedure)2. Hospital length of stay3. In patients who are never transferred to the ICU, the length of stay on the acute care floor4. ICU length of stay5. Proportion with readmission to hospital within 72 hours postdischarge6. In patients who meet the sepsis-2 criteria, the proportion of shock (ie, hypotension requiring inotropes or pressors), and death7. Number of days on intravenous antibiotics8. Number of days on intravenous anti-infectives9. Total duration of mechanical intubation (emergent and nonemergent)10. Impact of sex on outcome

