**Hypothesis 2**
1. Time of emergent intubation post-ICU transfer (emergent is defined by clinician’s notes as a nonplanned procedure)2. Time of the first order post-ICU transfer for transfusion of 3 units or more of blood ordered within 24 hours3. Time of first order post-ICU transfer of intravenous inotropes or pressors administered for shock (including septic shock)4. Time of cardiac arrest post-ICU transfer5. Time of congestive heart failure escalation, defined by the time of first order for diuretic drip, time of first order for continuous venovenous hemodialysis, or time of dialysis initiation6. Time of death post-ICU transfer7. “Infinite” event-free survival, defined as discharge from the ICU without an event

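### The zero-hour death rule has no 21-day limit and event-free discharge earns 504 hours whatever the destination, so the death component is death before discharge, not 21-day survival

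*Protocol article*

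**What the plan says.** All the rules at issue stand in the protocol article under Primary Hypothesis.

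- Window: "The primary outcome is the number of hours free from clinical deterioration (acute clinical events) within 21 days of admission".
- Ceiling: "A maximum score will be 21 event-free days (504 hours".
- Discharge: "Patients who are discharged from the hospital prior to 21 days without an event will be counted as having 21 event-free days (504 hours".
- Death: "Patients who die during the admission will be counted as having 0 event-free days (0 hours".
- Nonfatal event, by example: "a patient who has an emergent ICU transfer on hour 26 of their admission will have 25 event-free hours".
- Censoring: nonemergent ICU transfer, nonemergent surgery transfer, "or other transfer (change in bed assignment) because a change in bed assignment can result in a change in randomization allocation".

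The article mentions neither hospice nor transfer to another hospital. The only post-discharge outcome listed is "Proportion with readmission to hospital within 72 hours postdischarge". It belongs to Hypotheses 2 and 4 and does not enter the primary outcome.

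**The concern.** The primary score is meant to describe the 21 days after admission, but death is handled on a different clock. The zero rule runs to the end of the admission, however long that is. The discharge rule stops observation at the door and fills in the remaining hours as event-free. For some patients the score is therefore defined twice, with different values. For all patients, the death component depends on whether death comes before discharge.

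This matters more than usual because the trial is open. Randomization Process says that anyone in the hall or at the central station can see which beds display a score. Intervention Details has coordinators discussing trends on rounds for the intervention arm only. Staff who decide on discharge thus see the risk display in one arm. If that changed where dying patients spend their last days, the affected patients could move between 0 and 504, the two ends of the scale, with no deterioration prevented.

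**Working it through.** **The plan's own figures.** 21 × 24 = 504 hours, as stated. An event on hour 26 leaves 25 event-free hours, as stated.

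**The rules applied to example patients.**

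| Patient | Score by the 21-day window and discharge rule | Score by the death rule |
|---|---|---|
| Event-free, discharged day 5, dies elsewhere day 7 | 504 | does not apply |
| Dies in hospital day 7 | – | 0 |
| Event-free to day 21, dies in hospital day 25 | 504 | 0 |
| Emergent ICU transfer on hour 26, discharged alive | 25 | does not apply |
| Emergent ICU transfer on hour 26, dies in hospital day 25 | 25 | 0 |

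The third and fifth rows each have two scores. The gap is the whole scale in the third and 25 hours in the fifth. The first two rows show that two patients who both die on day 7 can score 504 and 0. These results need no assumption.

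**Leverage of a shift in discharge practice.** If a proportion *p* of an arm moves from in-hospital death (0) to event-free discharge (504), the arm mean rises by *p* × 504.

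- *p* = 0.1%: 0.001 × 504 = 0.50 h
- *p* = 0.5%: 0.005 × 504 = 2.52 h
- *p* = 1%: 0.01 × 504 = 5.04 h

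These are upper bounds, because only a patient who is still event-free and uncensored at discharge gains the full 504. A patient with an emergent ICU transfer on hour 26 who is later discharged instead of dying in hospital moves from 0 to 25. At *p* = 0.1% that adds 0.001 × 25 = 0.025 h.

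**Scale, on assumptions.** Sample Size, Power Analysis, and Attrition gives 10,424 admissions and 11% dropout: 10,424 × 0.89 = 9,277, or about 4,639 per arm. The article gives no event rate or standard deviation. Assume that 5% to 10% of patients have any event, that 1% to 3% die (included in that figure), and that nonfatal event scores are uniform on 0 to 240 h.

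- 5% events, 1% deaths: mean = 0.95 × 504 + 0.04 × 120 = 483.6 h; variance = 0.95 × 504² + 0.04 × 240²/3 − 483.6² = 8,214; SD = 91 h.
- 10% events, 3% deaths: mean = 0.90 × 504 + 0.07 × 120 = 462.0 h; variance = 0.90 × 504² + 0.07 × 240²/3 − 462² = 16,514; SD = 129 h.
- Detectable difference at 80% power, two-sided 5%, = SD × (1.96 + 0.84) × √(2/4,639), which is about 5.3 to 7.5 h.

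Dividing by 504, a shift of about 1.0% to 1.5% of an arm would match that difference. A 0.5% shift alone would reach significance in about 15% to 27% of trials. The calculation compares simple means and ignores clustering, which would lower these percentages. Over the four combinations examined (5% events with 1% or 2% deaths, 10% with 2% or 3%), deaths account for about 25% to 47% of the hours lost. Nonfatal events carry the other 53% to 75%.

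**The case against.** The strongest reply is that the governing sentence already sets 21 days and the scoring rules sit beneath it, so the death sentence merely fails to repeat the limit. The full 0-versus-504 conflict also needs an uncommon patient: 21 days with no event and no censoring bed change, then death in the same admission. Both remarks limit how often the conflict arises. Neither removes it, since the death rule as worded is tied to the admission.

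A second reply is that in-hospital scope looks deliberate. The Hypotheses 2 and 4 list counts events during the hospital stay, and the cost-effectiveness analysis uses in-hospital mortality. That is a fair reason to keep an in-hospital death component, provided it is described as one.

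Several stronger readings are tempting, but the documents do not support them.

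- *Every live discharge scores 504.* The rule requires discharge without an event, and the hour-26 example scores 25.
- *The endpoint measures place of death.* Textbox 1 lists four nonfatal components beside death, and on the assumptions above they carry more than half of the hours lost.
- *The display will move patients to hospice and create false benefit.* The article says nothing of the kind. It describes the display's purpose as further attention, diagnostics or escalation. A rule applied alike in both arms biases the comparison only if discharge practice differs between them.
- *Transfer to another acute hospital scores 504.* It might be a censored other transfer, although the gloss about bed assignment points to moves within the hospital. The article leaves this open, and the full protocol may settle it.
- *The Hypothesis 2 item on infinite event-free survival repeats the fault.* It belongs to a separate secondary analysis and can be read as confined to the ICU episode.

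**Conclusion.** The point holds in two parts. First, as written, the 21-day window and the unlimited death rule give two different scores to some patients who die in hospital after day 21, with a gap of up to 504 hours. This follows from the text alone. Second, the death component is death before discharge and not 21-day survival, so the primary score is open to any difference between arms in how dying patients are discharged.

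The size of the second part cannot be known from the article, which gives no rate of death, hospice discharge or interhospital transfer. The firm figure is the leverage: at most 0.5 h on an arm's mean for each 0.1% of that arm shifted. Set against an assumed detectable difference of 5.3 to 7.5 h, shifts of a few tenths of a percent would matter but would not usually decide the trial. Severity is moderate: the primary score needs a clear definition, but the endpoint as a whole is not invalid.

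**What to change.** 1. Under Primary Hypothesis, restrict the zero-hour rule to deaths in hospital within 21 days of admission, and say that patients who die later are scored on their events up to day 21.
2. Describe the death component as in-hospital death, so that it is not read as 21-day mortality.
3. Prespecify a sensitivity analysis that scores event-free discharge to hospice as death (0 h), using discharge disposition from the clinical data warehouse.
4. State whether transfer to another acute hospital falls under the discharge rule or the censoring rule. If it is censored, note that censoring a transfer made because of deterioration is informative.

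The hospice scoring belongs in a sensitivity analysis. In the primary analysis it could bias the result the other way if the display led patients who would otherwise have gone home to enter hospice.

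The cost is a few sentences, one extra extracted field and one extra analysis. The wording should be settled before any unblinded comparison, including the planned interim analysis. If the full protocol already defines these rules, its wording should be checked against the four items.
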